## 2.3 Primary Outcome

Change in weight from pre-bariatric surgery weight.

## 2.4 Secondary Outcomes

1. Incidence of physical and psychological comorbidity in a population seeking bariatric surgery

In the 3 years following bariatric surgery:

2. Change in weight/BMI from pre-bariatric surgery weight
3. Rate of incident type 2 diabetes
4. Change in incidence of depression and anxiety compared to baseline level pre-operatively
5. Incidence of complications immediately post-operatively and the need for readmission for revisional procedures
6. Change in health-related quality of life compared to baseline level pre-operatively
7. Change in glycaemic control, cardiovascular risk factors, CKD, retinopathy and medications prescribed in patients with diabetes compared to equally obese patient with diabetes who did not have bariatric surgery
8. Cost of the procedure and follow-up

Outcomes, including their source and frequency of measurement, are summarised in table 1.

## Surgical Obesity Treatment Study

2017\_11\_22 SCOTS Protocol v1.6

Page 26 of 61

Glasgow Clinical Trials Unit

### 3 STUDY DESIGN

#### 3.1 Overview of study design

This 3 year prospective cohort study will collect data on the medium term outcomes of bariatric surgery in a minimum of 400 individuals. The study will be performed according to the Research Governance Framework for Health and Community Care (Second edition, 2006) (12). The information required to meet the objectives will be collected by a combination of sources including: bariatric surgery specific information entered by clinical teams; data linkage to routine clinical data and patient reported outcome measure questionnaires (PROMS). The outcomes and the data source are described in detail in Table 3-1.

TABLE 3-1: PRIMARY AND SECONDARY OBJECTIVES OF SCOTS DESCRIBING SOURCES OF OUTCOME DATA

|     | Outcome                                                                                                                           | Data source                                                                                            | Frequency                                                              |
|-----|-----------------------------------------------------------------------------------------------------------------------------------|--------------------------------------------------------------------------------------------------------|------------------------------------------------------------------------|
| 1   | Incidence of physical and psychological comorbidity in a population seeking bariatric surgery.                                    | SCI-DC Scottish National dataset, eDRIS at National Service Scotland, Patient reported questionnaires. | Continuous throughout study                                            |
| 2.1 | Change in weight/BMI from pre-bariatric surgery                                                                                   | Clinical teams                                                                                         | At recruitment, annual check up                                        |
| 2.2 | Rate of incidence of type 2 diabetes                                                                                              | SCI-DC Scottish National dataset                                                                       | Continuous throughout study                                            |
| 2.3 | Change in incidence of depression and anxiety compared to baseline levels pre-operatively                                         | eDRIS at National Service Scotland, Patient reported questionnaires                                    | Pre-operatively, ,2,3 years post operatively                           |
| 2.4 | Incidence of complications immediately post-operatively and the need for revisional procedures                                    | Patient reported questionnaires, surgical teams                                                        | Pre-operatively, 2, 3 years post operatively, at time of re-operation. |
| 2.5 | Change in health related quality of life compared to baseline                                                                     | Patient reported questionnaires                                                                        | Pre-operatively, 2,3years post operatively                             |
| 2.6 | Change in glycaemic control, cardiovascular risk factors, chronic kidney disease (CKD), retinopathy, medications in patients with | SCI-DC Scottish National dataset                                                                       | Pre-operatively, 2, 3 years post operatively, at time of re-operation. |

Surgical Obesity Treatment Study

2017\_11\_22 SCOTS Protocol v1.6

Page 27 of 61

## Glasgow Clinical Trials Unit

|     |                                                                             |                                                                         |                                                                        |
|-----|-----------------------------------------------------------------------------|-------------------------------------------------------------------------|------------------------------------------------------------------------|
|     | diabetes compared with non-obese cohort                                     |                                                                         |                                                                        |
| 2.7 | Cost of the procedure and follow-up (to inform cost effectiveness analysis) | Clinical teams, e-prescribing record linkage, patient reported outcomes | At time of patients operation, continuous linkage throughout the study |

This protocol describes the objectives of the study, the sources of data collection for each objective, and the input required from patients and clinical teams throughout the study. A data collection portal will be developed for the study with secure logins for clinical teams and participating patients. A detailed user manual will be developed for the operation of this system will be produced by the Robertson Centre for Biostatistics - University of Glasgow.

A SCOTS web based portal will be developed which will present information on the study to the public and other researchers. The portal will contain secure logins to the Robertson Centre databases which will allow clinical teams to enter data. Clinical teams will be asked to register for a user ID and password. These will be issued once the team have undergone the necessary training for their delegated role. Everyone who has a user ID and login will be a member of the SCOTS investigators group.

The SCOTS portal will include an area which will allow patients who have agreed to complete the patient questionnaires to login securely and complete the patient reported outcome questionnaires. If patients prefer to complete the questionnaires on paper the data will be entered by staff at the Robertson Centre into the database. Patients will be kept up to date with progress of the study via updates on the study website. Patients will be sent reminders through their preferred route of communication to let them know when they are due to complete a questionnaire.

Patient identifiable information will be stored separately from the clinical outcome data. The information will be linked using a database code. Within the Robertson Centre individuals who can access patient information to send reminder letters will not have access to any clinical information. Any clinical information to be analysed will have all patient contact details remove. Production of any reports will follow the NHS Information and Statistics division (ISD) Statistical Disclosure Control protocol (13) to ensure that patient confidentiality is maintained, (this is a requirement of the record linkage arrangement with ISD).

SCOTS has three distinct parts. All adult patients who are having weight loss surgery in Scotland will be invited to participate in three parts of the study. These parts are described in detail below.

## Surgical Obesity Treatment Study

## Glasgow Clinical Trials Unit

### 3.1.1 Part 1 Record Linkage

The study will collect data by record linkage to patients' clinical outcomes. Information will be recorded by the clinical team on the operation they have had. They will be followed using their medical records until at least December 2020 and if funding is available for the rest of their life. This will include all hospital admissions, blood test results, diagnostic test results, diabetes complications, medications they are prescribed, pregnancy, psychiatry and mortality. This part of the study will observe patients care. The study will not alter their planned care in any way. No additional tests or treatments will be given to patients who consent to be part of the study. (This will fulfil the primary objective and objectives 1, 2, 3 and 4). If patients do not consent to participate in this part of the study they will not be asked to participate in Part 2 or Part 3.

Each record linkage requires approvals to access data including a favourable ethical opinion. These will be sought by the SCOTS Project team. A separate procedure for each data linkage will be developed by the Robertson Centre for Biostatistics. Patient identifiable information is required to identify study participants. The information required is patient CHI number, family name, given name, patient date of birth, gender, postcode, consent data and unique study identifier.

### 3.1.2 Part 2 Patient Reported Outcomes (PROMS) Questionnaire

We will ask patients if they are willing to complete a questionnaire which will include questions on quality of life, overall health and fitness, diet, and anxiety and depression, healthcare utilisation and ability to work. They will also be asked about problems they may have experienced since their surgery such as pain and surgical site infection post discharge.). Where patients are not completing PROMS and there is no reliable clinical weight record, we will write after 3 years requesting completion of a weight questionnaire (simply asking their current weight). The patients will be offered a voucher based incentive of £30 for completing both the year 2 and 3 questionnaires (high street voucher), and £10 for the year 3 weight follow-up questionnaire (for those no longer in clinical follow-up/not completing PROMS)

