## Glasgow Clinical Trials Unit

3. The effect of surgical experience and the pre and post-operative care pathway on complication rates and weight loss, for different bariatric surgical procedures.
4. The effect of the pre-surgical pathway and criteria on bariatric surgery patient selection. Change in health related quality of life, anxiety and depression over time pre- and post-operatively for a mean of 3 years from date of bariatric surgery.
5. The weight status pre and post-operatively for 3 years after bariatric surgery.
6. The glycaemic control, lipids, blood pressure, medication prescription, and rate of diabetes complications (microalbuminuria and renal disease, and retinopathy) in those that have pre-existing diabetes or develop diabetes for 3 years follow up since bariatric surgery.
7. Changes in socio-economic factors (employment, benefit receipt, sick leave, and health care use) for 3 years since bariatric surgery.

All the above objectives are due to be achieved by December 2020 (Start Jan 2012, 2 years development, 3 years recruitment finishing March 2017, mean 3 years post-operative follow-up finishing December 2020).

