## Surgical Obesity Treatment Study

## Glasgow Clinical Trials Unit

If the research team does not receive the completed consent form from the patient within two weeks and cannot reach the patient by telephone, a follow up letter should then be sent.

9. On receipt of the signed form, the person that obtained informed consent signs and dates the consent forms adding their name in block capitals.
10. If a witness is required they can also sign and date the consent form (this may be in the case where an interpreter is required).
11. One copy of the form should be provided to the patient (posted back in case of SCOTS team recruitment), one filed in the patient's notes and one copy stored in the site folder, and a copy sent to the Robertson Centre for the study files. A copy of the version of the patient information leaflet which was given to the patient should be filed within the site study file.
12. If the patient consents to the study the patient recruitment form should be completed with the patient via the telephone. Record patient name and CHI number (for NHS patients), sex, height and weight.
13. Patients should be asked for their contact details including their e-mail and mobile phone contact details and ensure that they identify their preferred route of communication.
14. The Patient recruitment form will be sent to the Robertson Centre and a copy filed within the site study file; When they are sent to the Robertson Centre a form will be faxed to show what documentation has been sent in the post, this will be recorded in a postage log.
15. The Letter to Inform Surgeon of Participation should be completed and sent to the surgeon along with the relevant operation details recording form.
16. Paper copies of the screening log are returned to the Robertson Centre annually, in self addressed envelopes provided by the SCOTS project team. These will also be recorded in a postage log.

|                                                                          |  |
|--------------------------------------------------------------------------|--|
| Checklist:                                                               |  |
| Check patient name and date of birth correct on patient recruitment form |  |
| Consent form signed and dated at each point                              |  |
| Patient sent copy of signed consent form                                 |  |
| Copy of consent form filed in notes                                      |  |

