## Glasgow Clinical Trials Unit

| PROMS                                                                 | Total |      | Total |    | Validated | baseline | 2 year | 3 year | Total |
|-----------------------------------------------------------------------|-------|------|-------|----|-----------|----------|--------|--------|-------|
|                                                                       | Total | Male | Femal |    |           |          |        |        |       |
| About you                                                             |       |      |       |    |           |          |        |        |       |
| Demographics – Essential                                              | 1     | 1    | 1     | P  | 1         | 1        | 1      | 1      | 3     |
| Marital Status                                                        | 1     | 1    | 1     | 1  | 1         | 1        | 1      | 1      | 3     |
| Ethnicity                                                             | 1     | 1    | 1     | 1  | 1         | 0        | 0      | 0      | 1     |
| Education                                                             | 1     | 1    | 1     | 1  | 1         | 0        | 0      | 0      | 1     |
| Occupation                                                            | 1     | 1    | 1     | P  | 1         | 1        | 1      | 1      | 3     |
| Health History                                                        |       |      |       |    |           |          |        |        |       |
| Your Medical History                                                  | 1     | 1    | 1     | 1  | 1         | 0        | 0      | 0      | 1     |
| Your Weight History                                                   | 1     | 1    | 1     | 1  | 1         | 0        | 0      | 0      | 1     |
| Family History                                                        | 1     | 1    | 1     | P  | 1         | 0        | 0      | 0      | 1     |
| Family History of Obesity                                             | 1     | 1    | 1     | 0  | 1         | 0        | 0      | 0      | 1     |
| Quality of Life                                                       |       |      |       |    |           |          |        |        |       |
| SF-12 v2 –licence required                                            | 1     | 1    | 1     | 1  | 1         | 1        | 1      | 1      | 3     |

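### Weight change, the primary outcome, has no time point, probably mixes telephone and clinic baselines, and as worded may go uncollected at year 3 in questionnaire completers who have left clinic

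*Protocol*

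**What the plan says.** **Definition.** Protocol Section 2.3 gives the primary outcome as "Change in weight from pre-bariatric surgery weight", and the synopsis does the same. Neither states a time. Section 2.4 repeats the variable as secondary outcome 2, "Change in weight/BMI from pre-bariatric surgery weight", under the lead-in "In the 3 years following bariatric surgery". The weight objective in Section 2.2 reads "The weight status pre and post-operatively for 3 years after bariatric surgery".

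**Source.** Table 3-1, row 2.1, names clinical teams as the only source and gives the frequency as "At recruitment, annual check up".

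**Baseline.** Section 4.2.3.1 (local recruitment) has the recruitment form, including height and weight, filled in with the patient present. Section 4.2.3.2, step 12 (research-team recruitment) says "If the patient consents to the study the patient recruitment form should be completed with the patient via the telephone", and height and weight are again on the form. Table 4-1, contact 2, covers both routes and has the clinical team and patient record baseline height and weight. Section 7.1.2 assigns height and weight at recruitment to the clinical teams.

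**Year 3.** Weights come from routine clinic visits (Section 4.2.6). The back-up in Section 3.1.2 is a one-question letter: "Where patients are not completing PROMS and there is no reliable clinical weight record, we will write after 3 years". The £10 voucher text in Sections 3.1.2 and 4.2.4 joins leaving clinical follow-up and not completing PROMS with a slash. In Table 17-1 the only named weight set is "Your Weight History", asked at baseline only.

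**The concern.** These matters are fixed in the protocol itself: what the primary outcome is, who supplies it, and who receives the letter. Three things follow from the wording.

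First, a patient who returns the questionnaires but no longer attends the surgical clinic fails one of the letter's two conditions, so no letter goes out. If the questionnaire does not ask for weight, the primary outcome is lost in a patient who is reachable and willing.

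Second, a baseline taken by telephone and a follow-up taken on clinic scales would be combined in one change score. Recruitment mode belongs to the site, so any error from it would be entangled with the care-pathway effect on weight loss in secondary objective 3.

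Third, without a time point a year-1, year-2, year-3 or last-available weight would each satisfy Section 2.3.

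**Working it through.** The protocol gives no SD, effect size, missingness rate or telephone share for weight, and its power statement in Section 5.3 concerns HbA1c and quality of life. There is no figure for weight to reproduce. The check is therefore a comparison of the text, followed by a range under stated assumptions.

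**1. Who is asked for weight at year 3, reading Section 3.1.2 as written**

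| Completes PROMS | Reliable clinic weight | Year-3 weight |
|---|---|---|
| Yes | Yes | Clinic |
| No | Yes | Clinic |
| No | No | Letter |
| Yes | No | No named route |

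For the fourth row, Table 17-1 gives "Your Weight History" a row total of 1, against 3 for sets asked on all three occasions. The table's overall totals, 30 + 23 + 22 = 75, fit baseline, year 2 and year 3. The set called Demographics – Essential is asked on all three occasions, but its items are not listed.

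**2. Time point.** Synopsis: participation runs for 3 years or to December 2020, whichever comes first. Section 2.2: recruitment finished in March 2017. Schedule of assessments: the recruitment visit can be up to 1 year before surgery. The latest surgery is then about March 2018, and 3 years later is March 2021, after collection stops. Anyone operated on after December 2017 cannot reach 3 years. How many such patients there are is not stated. Follow-up can thus be unequal, and the choice of time point affects the result.

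**3. Mixed-mode baseline**

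Inputs: n = 400 (Section 5.3). Assumed: share recruited by telephone f = 10-50%; under-statement u = 1-3 kg; SD of weight change 12-20 kg; follow-up measured in clinic.

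- Standard error of the mean change = SD/√400: 12/20 = 0.60 kg and 20/20 = 1.00 kg.
- Shift in mean loss = f × u: 0.10 × 1 = 0.1 kg to 0.50 × 3 = 1.5 kg, with loss understated.
- In standard errors: 0.1/1.00 = 0.1 to 1.5/0.60 = 2.5.
- Between telephone and clinic sites: the whole of u, 1-3 kg.

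The direction is not fixed. A measured baseline with a patient-stated year-3 weight overstates loss. If both ends are patient-stated, the errors partly cancel.

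**4. Missing year-3 weights**

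Assumed: a share m = 10-50% is missing, and those patients lost g = 3-10 kg less than the rest.

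- Overstatement of mean loss = m × g: 0.10 × 3 = 0.3 kg to 0.50 × 10 = 5.0 kg.
- 95% half-width in SD units = 1.96/√n: 1.96/√400 = 0.098 with none missing; 1.96/√200 = 0.139 with half missing.

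These figures cover all missing weights. Only the fourth row of the table is avoidable by changing the letter rule.

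**The case against.** The strongest reply is that the year-3 gap is not proven. Table 17-1 lists sets of questions, not items. Demographics – Essential is coded as partially validated, meaning questions were added to a published set, and a weight question could be among them. Sending a weight-only letter just to non-completers would make sense if completers already gave their weight. The slash in the voucher text could also mean either condition. All this stands, so a reader who infers that completers are certainly asked for everything except weight goes too far. But neither reading clears the text. If the questionnaire does collect weight, Table 3-1's single source is incomplete. If the slash means either condition, it conflicts with the trigger sentence. The letter itself is already a source that Table 3-1 omits.

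On baseline, the protocol never describes the telephone weight as self-reported, and these patients have also attended a clinic. Self-report is a probable inference. What is certain is that Section 4.2.3.2 does not sit with Table 4-1, Section 7.1.2 and Table 3-1.

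On size, a reader might set 1-3 kg against a standard error of 0.60-1.00 kg and conclude 1-5 standard errors. That holds only if every patient has exactly one patient-stated weight, and nothing in the protocol suggests so.

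On the time point, the study declares objectives rather than hypotheses, its follow-up is 3 years throughout, and secondary outcome 2 adds BMI. The omission is real but takes one sentence to cure. Adjustment for weight source and a measured-only sensitivity analysis belong in the SAPs that Section 5.1 announces; their absence here is not a fault.

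**Conclusion.** The point holds as a risk. The wording supports three statements: the primary outcome has no time point; baseline weight is collected differently by recruitment route, with sections that disagree on who supplies it; and the letter's double condition leaves questionnaire completers without a clinic weight with no named route to a year-3 value. It does not support saying that the outcome will be biased or will be missing, because the telephone share, the reporting error and the follow-up questionnaire's items are not given.

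Under the assumed ranges, the baseline problem moves the overall mean by about 0.1-1.5 kg (0.1-2.5 standard errors at n = 400). The larger exposure is the comparison between sites, where the full 1-3 kg could appear as a pathway effect. This should be fixed, with moderate confidence. The year-3 item is the most pressing, since a weight not requested at the time cannot be fully recovered later.

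**What to change.** 1. Section 3.1.2: at year 3, request current weight from everyone without a reliable clinic weight, whatever their PROMS status. Alternatively, add one current-weight item to the 2- and 3-year questionnaires, or state that one is already there. Align the voucher wording in Sections 3.1.2 and 4.2.4.
2. Section 4.2.3.2: reconcile with Table 4-1 and Section 7.1.2 by taking the clinic-recorded pre-operative weight as baseline for telephone recruits, from the pathway point named in the title of Figure 4-1. Retrieve it at the site visits that Section 7.1.3 already schedules at least yearly.
3. Record the source of every weight (measured or patient-stated), and list all sources in Table 3-1.
4. Section 2.3 and synopsis: name 3 years as the time point of the primary outcome.

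Cost: one questionnaire item, or some extra letters with their £10 vouchers; record look-up at visits already planned; and a few changed sentences. No extra patient visit or procedure is needed.
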